### Passive cohort

All children up to 36 months of age residing in enumerated households during the census will be eligible for inclusion in the passive cohort and enrolled upon provision of written informed consent from their primary caregiver (Table 1). Enrolled children will be passively monitored to record both EPI vaccinations and PMC visits as well as clinical visits for malaria and anaemia to the health facility and/or CHWs over the 18-month study period. Older children (24 to 36 months at baseline) are not eligible to receive the intervention but will be enrolled in this study activity for two reasons: first, the older children will serve as an internal control as it is assumed that they will experience a similar malaria transmission intensity but will not receive the intervention and, secondly, as children will be followed for 18 months information will be available on children who age-out of eligibility to assess any impact beyond when children are eligible to receive PMC. Children will not be censored according to age.

During the passive cohort recruitment, trained fieldworkers will record basic demographic information about the child, recent malaria cases, amongst other information. An anonymous and unique QR code with the participant ID linked will be attached to each child’s health and vaccination record books. This QR code will be used to identify children participating in the study when they interact with the health system and facilitate linking the data generated by the routine system on EPI, PMC or clinical visit, which are stored in separate registers, with the research activities. During recruitment, the national health ID number assigned to each child and written in the health and/or vaccination record books will be recorded. The names of children and primary caregivers will also be recorded to provide a means to verify that children present match ID numbers. This also serves as a back-up method to link health information data that is routinely collected in different registers. Caregivers will be encouraged to take children to the participating facilities or CHWs to receive EPI vaccinations or PMC or for any illnesses.

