### Active cohort

The active cohort will measure malaria infection, anaemia, and malnutrition incidence in the intervention and control study populations in Cameroon and Côte d’Ivoire. The sampling frame for the active cohort will consist of the children whose primary caregiver provided consent for participation in the passive cohort (Table 1). Children between 6 and 9 months and 10 weeks and 6 months of age at recruitment in Cameroon and Côte d’Ivoire, respectively, will be approached for inclusion. Targeting these age ranges will maximize study power to measure differences between the PMC intervention and standard of care in each country within the 18-month study period. The target age range was also defined to ensure at least one sampling time point after the final potential PMC dose to observe any change in risk of malaria infection after aging out of the intervention [13]. Recruitment into the active cohort will continue until the target sample size is achieved.

At the initial household visit for children enrolled in the active cohort, field workers will record the household and child ID number assigned during the census and collect detailed information related to malaria risk factors including household construction and use of vector control interventions. A detailed questionnaire on recent fevers, malaria history, care seeking behaviours, EPI vaccines received to date, and other relevant factors will also be collected. Children will be assessed for fever, anaemia, malaria, and malnutrition. First, forehead temperature will be taken using an infrared thermometer with fever defined as those with temperature > 37.5 °C. A capillary blood sample by heel or fingerpick will be collected using a sterile lancet and aseptic technique on all children. The blood sample will be used to measure: (i) haemoglobin (Hb) levels with a photometer (HemoCue^®^ Hb 301, Angleholm, Sweden), devices, (ii) conduct a malaria rapid diagnostic test (RDT), (iii) prepare a thin and thick blood slide for malaria microscopy and (iv) to collect blood spots on filter paper. The mid-upper-arm circumference will be collected from all enrolled children to screen for malnutrition and monitor growth trajectories over time. Treatment for malaria, anaemia and malnutrition will be offered according to national guidelines. Any children with a fever or who are severely ill will be referred to the nearest health facility for treatment.

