Each child in the active cohort will be followed-up for a maximum of seven visits at three-monthly intervals over 18 months, including the initial recruitment visit plus six subsequent follow-up visits (Fig. 4). During follow up visits at the household, verbal consent from the primary caregiver for continued participation of their child in the study will be recorded. A short questionnaire will be completed to collect data about any malaria or anaemia diagnosis or receipt of PMC since the last study visit, at which health facility care was sought and other relevant information. A blood sample will be collected following the same procedures outlined above.

Adverse events and safety of receiving PMC will be monitored by the MoH as part of the routine programmatic implementation of this intervention. Participant safety will be monitored throughout the study period and any adverse effects related to study procedures will be investigated using standardised procedures and managed according to national guidelines.

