### Data analysis

The primary analysis will be based on intention to treat (ITT), including all children residing in the intervention area as the exposed group. All available data up to the time of censuring (e.g., loss to follow-up, withdrawal, death, or study completion), irrespective of whether the child received any, part, or all the intended PMC doses. An additional per-protocol analysis will be completed which includes children who received at least one dose, all doses, or specific doses of PMC. The period of protection provided by SP is up to one-month post treatment and thus will constitute the protective window of those receiving the intervention. Data for both countries will be combined for analysis as well as assessed separately to ensure context specific nuances are fully assessed.

Incidence rates for malaria and anaemia will be calculated using multivariable Poisson regression, difference-in-difference, and interrupted time-series models comparing intervention and control areas [14–16]. Incidence rates, rate differences, and rate ratios between intervention and control area will be calculated for the ITT and per-protocol analysis. Malaria incidence will be determined by the number of malaria cases confirmed by either RDT or microscopy identified in either the passive or active cohort. Person-time at risk for each study outcome will be calculated based on the date of recruitment into the study population until the date of censuring or study end. For children who leave the study prior to the end date, the date of exit will be the date where they moved, withdrew from the study, or died. If that date is not known, the midpoint between the date of last contact and the date the loss was detected will be used. Protective effectiveness will be calculated for the intervention period including the 18 months of follow-up for the periods where PMC doses differ, stratified by first and second year of life, as well as during the post-intervention period, starting at 24 or 18 months of age in Cameroon and Côte d’Ivoire, respectively, to estimate any potential rebound in malaria.

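### One exit rule for every outcome adds unobservable time to outcomes seen only at household visits, understating those rates by about 2% at the planned loss

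*Protocol article*

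**What the plan says.** The Data analysis section of the Protocol article gives a single definition: "Person-time at risk for each study outcome will be calculated based on the date of recruitment into the study population", running to censoring or the end of the study. For children who leave early, "the date of exit will be the date where they moved, withdrew from the study, or died". For undated exits it adds: "If that date is not known, the midpoint between the date of last contact and the date the loss was detected will be used". Neither sentence distinguishes between cohorts or outcomes.

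The two cohorts observe different things. In the Active cohort section, "The active cohort will measure malaria infection, anaemia, and malnutrition incidence in the intervention and control study populations", with children followed for "a maximum of seven visits at three-monthly intervals over 18 months". Infection is tested, haemoglobin measured and arm circumference taken at those household visits. In the Passive cohort section, "Enrolled children will be passively monitored to record both EPI vaccinations and PMC visits as well as clinical visits for malaria and anaemia", using facility and community health worker contacts. Malaria incidence combines the two sources: it counts "malaria cases confirmed by either RDT or microscopy identified in either the passive or active cohort".

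**The concern.** Person-time belongs in a rate's denominator only while an event could enter its numerator. For a register-based outcome, a child who is still resident can have a recorded case up to the day of departure, so a midpoint guess at an unknown departure date is reasonable. For an outcome that exists only if a fieldworker tests or measures the child, observation stops at the last completed visit. Time from then to the midpoint, or to a known later exit date, cannot contribute an event.

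Two things are at stake. Absolute rates of the visit-only outcomes are pulled down in proportion to loss. The comparison between areas is also distorted if loss differs between them. The areas were purposively chosen rather than randomised, so equal loss cannot be taken for granted.

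**Working it through.** **The plan's own figures.** The only stated figures that use the loss rate are the active-cohort sample sizes, and this point does not dispute them. The children factor exactly: 26 × 60 = 1,560, 9 × 60 = 540, 14 × 82 = 1,148 and 5 × 82 = 410. The facility counts come out of the Hayes–Bennett formula for rates,

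c0 = (z_α/2 + z_β)² × [(λ0/y + k²λ0²) + (λ1/y + k²λ1²)/r] / (λ0 − λ1)²,

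with two-sided 5%, 80% power and r = 3. Here y is 80% of the children per facility × 1.5 years. I assume that the stated 0.25 acts as a between-cluster coefficient of variation k, and that the baseline rates are the 2020 incidences of 0.597 and 0.572 per child-year.

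- Cameroon (30% reduction): c0 = 8.84 control and 26.5 intervention (stated 9 and 26); power 80.5%.
- Côte d'Ivoire (40% reduction): c0 = 4.48 and 13.4 (stated 5 and 14); power 83.8%.

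**Inputs for the exit rule**

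- Loss L = 20%, not split by area (Sample size).
- Visits every 3 months over 18 months (Active cohort); census updates also every 3 months (Census).
- Assumptions: losses spread evenly over the six intervals; last contact is the last household visit; every exit date is unknown.

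**Formulas, in months per recruited child**

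- A lost child was last seen at month 0, 3, 6, 9, 12 or 15, on average 7.5.
- Observed time: O = (1 − L) × 18 + L × 7.5.
- Time under the rule: R = O + L × g/2, where g is the gap from last contact to detection of the loss.
- Rate factor: f = O/R.

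**Effect on rates at L = 20%**

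- O = 14.4 + 1.5 = 15.9.
- g = 3: R = 15.9 + 0.3 = 16.2; f = 0.981. The denominator is 1.9% too large and the rate about 1.9% too low.
- g = 6: R = 15.9 + 0.6 = 16.5; f = 0.964, a rate 3.6% too low. This is slightly generous, because a child last seen at month 15 cannot be detected six months later within an 18-month study. With 1.5 months added for that child, the mean addition is (5 × 3 + 1.5)/6 = 2.75, R = 16.45 and the rate is 3.3% too low.
- In child-months with g = 3: Cameroon 0.2 × 1,560 × 1.5 = 468 and 0.2 × 540 × 1.5 = 162; Côte d'Ivoire 0.2 × 1,148 × 1.5 = 344 and 0.2 × 410 × 1.5 = 123.

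**Effect on the rate ratio**

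Equal loss gives the same f in both areas, so the ratio does not change. For an assumed 10% versus 30%:

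- g = 3: f = 16.95/17.10 = 0.9912 and 14.85/15.30 = 0.9706; ratio 1.021.
- g = 6: f = 16.95/17.25 = 0.9826 and 14.85/15.75 = 0.9429; ratio 1.042.

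| True ratio 0.70 | g = 3 | g = 6 |
|---|---|---|
| Loss 10% intervention, 30% control | 0.715 | 0.730 |
| Loss 30% intervention, 10% control | 0.685 | 0.672 |

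**Does the repair touch the sample size?** No. The calculation that reproduces the facility counts credits 0.80 × 18 = 14.4 months per recruited child. Ending time at the last visit leaves 15.9.

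**The case against.** The strongest reply is that the midpoint is a common convention for unknown exit dates, and that the main endpoint is mostly outside the problem. Malaria incidence takes cases from either cohort, so time after the last visit can still yield a facility or community health worker case. Anaemia episodes are also captured passively. This stands, and it is why the stated rule should remain for passive outcomes. It does not rescue visit-detected infection, measured haemoglobin or malnutrition.

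The size is also fairly called small. The calculation takes every exit date as unknown, and the midpoint applies only then. Known dates that fall soon after the last visit reduce the effect. They do not remove it, because a known date late in an interval adds up to 3 months, the same as the six-month case.

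A reader might infer three stronger things that the article does not support.

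- **Loss detected only at study end**, giving larger distortions. This conflicts with three-monthly visits and three-monthly census updates.
- **Missed middle visits counted as wholly unobserved time.** The follow-up questionnaire asks about diagnoses since the previous visit and passive capture continues, so such gaps are partly covered.
- **Declining household visits ends passive follow-up.** At each follow-up visit, "verbal consent from the primary caregiver for continued participation of their child in the study will be recorded", and withdrawal from the study is an exit date. But nothing in the article treats refusal of visits as such a withdrawal. Table 1 and the Passive cohort section give the passive cohort its own consent, and the recording of partial refusal is ordinary detail for the full protocol or operating procedures.

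**Conclusion.** The point holds in a limited form. A rule stated for every outcome does not fit those that only a completed household visit can reveal. At the planned 20% loss it understates their rates by at most about 2% when loss is detected at the next three-monthly visit, and by about 4% with a six-month gap. These figures rest on evenly spread loss and unknown exit dates.

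The rate ratio is unaffected by equal loss. It shifts by about 2% under an assumed 10% versus 30% split, in either direction; the article gives no split by area. The passive outcomes are not affected, and the combined malaria incidence is affected only through its visit-detected component. This is a small error in a stated rule, worth correcting because the correction is nearly free.

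**What to change.** In the Data analysis section, define the end of person-time by how the outcome is detected:

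- **Visit-only outcomes** (visit-detected malaria infection, measured haemoglobin or anaemia, malnutrition): end at the last completed household visit, whether or not the exit date is known.
- **Passively detected outcomes, and the passive component of combined malaria incidence:** keep the stated exit date and midpoint rule, so that validly observed passive time is not discarded.

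The cost is a change of analysis wording and slightly less active-cohort person-time, from 16.2 to 15.9 months per child on the figures above. Data collection and sample size do not change.

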### Study design

All health facilities providing EPI services in selected study sites and corresponding catchment populations will be eligible for inclusion and constitute the primary sampling unit for this evaluation. Health facilities will be randomly selected for inclusion (Fig. 3). All non-EPI/PMC facilities within the selected EPI catchment areas, will be included in the passive cohort data collection, described below (Table 1). In the selected EPI facility catchment areas, several study activities will be conducted: (i) a census to enumerate all households, primary caregivers and children under 36 to characterize the population eligible to receive PMC (0–24 months) as well as when they age out of the intervention (25–36 months), (ii) a passive cohort at health facilities to monitor clinical episodes of malaria and anaemia as well as receipt of EPI vaccinations and PMC in children under 36 months, and (iii) to monitor malaria and anaemia in a subgroup of participating children in an active cohort over an 18-month period. The same procedures will be employed in both intervention and control areas in Cameroon and Côte d’Ivoire.

**Table 1 Tab1:** Eligibility criteria for each study component in the PMC impact evaluation study

	Inclusion Criteria	Exclusion Criteria
**Health Facilities**	- Located within the target study sites - Administer EPI/PMC services	- Located outside of the target study area
**Census - Household**	- Located within the catchment area of selected health facilities - Head of household provides consent	- Located outside of the selected health facility catchment area - Head of household not present or refuses participation
**Passive Cohort - Child**	- Regularly resides in households included in the census - Age 36 months or less at time of census - Primary caregiver provides informed consent	- Head of household refused participation in the census - Primary caregiver not present or refuses participation - Not expected to reside in the selected household for the study duration - Age greater than 36 months of age at recruitment visit

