### Sample size

For the passive cohort, we will monitor all eligible children enrolled in the study and will therefore, will constitute a population sample. For the active cohort, the sample size was calculated to ensure 80% power at the 5% significance level, assuming an intra-cluster correlation coefficient of 0.25, and accounting for a 3:1 sampling ratio of intervention to control to ensure sufficient power to assess any variation in PMC effectiveness according to distance to the EPI facility. However, the specific sample size for the number of EPI facilities and children to include in the active cohort was calculated separately for each study site to account for the differences in PMC implementation (Fig. 1).

In Cameroon, we expect a 30% reduction in malaria incidence in intervention compared to control areas, requiring 26 intervention and 9 control EPI facilities are required. With a 20% expected loss to follow-up rate, we require 1,560 in the intervention and 540 children in the control area over the 18 months of observation in the active cohort. In Côte d’Ivoire, the standard of care currently being implemented by the NMP is no doses, so the difference between in the number of SP contacts between arms is 5. Therefore, we expect a 40% reduction in malaria incidence in intervention compared to control areas. Accordingly, 14 and 5 EPI facilities will be required in the intervention and control areas, respectively. Assuming a conservative loss to follow-up rate of 20%, we require 1,148 and 410 children in the intervention and control areas, respectively, over the 18 months of observation in the active cohort.

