Where there are repeated measures per child, random effects or generalising estimating equations models will be used to adjust for non-independence of the data from the same individual. Regression models will assess factors associated with incidence of malaria infection including demographic variables, malaria history, reported vector control use, socio economic position, amongst others [17]. Transmission intensity, type of PMC delivery mode, impact of the estimated protective window of SP, and other factors will be adjusted for to assess their impact on the incidence trends [18]. Subgroup analysis will constitute assessing the impact of distance to the health facility as a proxy for access to health services according to the study endpoints highlighted above. Distance will be assessed according to tertials of distance of all study participants to their nearest health facility and as a continuous variable. Alternate model forms including interaction terms as well as semiparametric approaches to account for time-varying intervention effects to account for the expected 4-week prophylactic period of SP will be tested [19]. Because of the challenges in confirming cause of death in those who die in the community and the assumption that severe malaria cases will seek care at a health facility, only the passive cohort data will be used to assess these secondary outcomes [20]. An interim analysis will be conducted after the 4th active cohort visit and the study will be reported according to the ‘Strengthening the reporting of observational studies in epidemiology’ (STROBE) guidelines [21].

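### The stated adjustment for correlated data stops at the child, although the study samples and sizes by EPI facility; child-level area comparisons run as written would have standard errors that are too small

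*Protocol article*

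**What the plan says.** All from the protocol article:

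- **Study design.** EPI facilities with their catchment populations "constitute the primary sampling unit for this evaluation", and "Health facilities will be randomly selected for inclusion".
- **Sample size.** The active cohort is sized to "ensure 80% power at the 5% significance level", "assuming an intra-cluster correlation coefficient of 0.25", with a "3:1 sampling ratio of intervention to control". The requirement is given in facilities first: 26 intervention and 9 control in Cameroon, 14 and 5 in Côte d'Ivoire.
- **Data analysis, comparison.** The primary intention-to-treat analysis counts all children living in the intervention area as exposed. Areas are compared by multivariable Poisson regression, difference-in-difference and interrupted time-series models.
- **Data analysis, correlation.** Where a child has repeated measures, "random effects or generalising estimating equations models will be used to adjust for non-independence of the data from the same individual". No facility random effect, facility-level GEE cluster or cluster-robust variance is mentioned anywhere in the article.

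**The concern.** The design treats the facility as the unit that carries correlation, and the analysis text names a different unit, the child. A random effect or GEE cluster for the child accounts for repeated visits by that child. It still treats two children from the same catchment as independent. Intention-to-treat exposure does not vary within a catchment, so variation between facilities feeds directly into the error of the area rate ratio. A child-level variance leaves that component out.

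The covariates listed in the same section, such as transmission intensity and delivery mode, may explain some between-facility variation. They do not put the remainder into the standard error. The risk is that ordinary differences between catchments are reported as an effect of PMC, at the interim analysis as well as at the end.

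**Working it through.** **Inputs from the article.** Two-sided 5% level (two-sidedness assumed) and 80% power. In Cameroon, "we expect a 30% reduction in malaria incidence" (rate ratio 0.70); in Côte d'Ivoire, "we expect a 40% reduction in malaria incidence" (rate ratio 0.60). Children per facility: 1,560/26 = 540/9 = 60 in Cameroon and 1,148/14 = 410/5 = 82 in Côte d'Ivoire. After 20% loss, m = 48 and 65.6.

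**Assumed input.** The Sample size section gives no baseline rate. I use the 2020 under-5 rates in the Cameroon and Côte d'Ivoire site descriptions, λ = 0.597 and 0.572 per child-year, over T = 1.5 years. So λT = 0.8955 and 0.858.

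**Step 1: which reading of 0.25 reproduces the sample size?**

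- *As an intra-cluster correlation*, the design effect is 1 + (m − 1) × 0.25 = 12.75 (Cameroon) and 17.15 (Côte d'Ivoire). A Poisson rate comparison inflated by this has power of about 32% and 31% over 18 months. Across the variants tried (proportions or rates, 1 or 1.5 years, before or after loss) power lies between about 20% and 44%. The planned 80% is not reproduced.
- *As a between-facility coefficient of variation k* (Hayes–Bennett), the variance of the rate difference is λ0/(c0·m·T) + λ1/(c1·m·T) + k²(λ0²/c0 + λ1²/c1), with c0 control and c1 intervention facilities.
  - Cameroon: 0.000921 + 0.000223 + 0.002475 + 0.000420 = 0.004039. The difference is 0.1791, z = 2.82, and power is 80.5% (78.1% with a t reference).
  - Côte d'Ivoire: 0.001163 + 0.000249 + 0.004090 + 0.000526 = 0.006027. The difference is 0.2288, z = 2.95, and power is 83.8% (79.3% with a t reference).
  - On the normal formula, the smallest number of control facilities at 3:1 is 9 and 5, as stated. With a one-year horizon after loss it would be 11 and 6, so the match depends on the 18 months.

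On either reading, the sizing allows for facility clustering.

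**Step 2: shortfall if the analysis stops at the child, with k = 0.25.** Let v be the squared coefficient of variation between children, which a child-level random effect or GEE absorbs. The article gives no value, so I show 0 to 2. With equal rates in both areas, set at the control value:

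variance ratio = 1 + k²·m·λT / (1 + v·λT)

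SE factor = √(variance ratio); type I error = 2[1 − Φ(1.96 / SE factor)]

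Here k²·m·λT = 0.0625 × 48 × 0.8955 = 2.6865 (Cameroon) and 0.0625 × 65.6 × 0.858 = 3.5178 (Côte d'Ivoire).

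| v | Cameroon: ratio, SE factor, type I | Côte d'Ivoire: ratio, SE factor, type I |
|---|---|---|
| 0 | 3.69, 1.92, 31% | 4.52, 2.13, 36% |
| 0.5 | 2.86, 1.69, 25% | 3.46, 1.86, 29% |
| 1 | 2.42, 1.55, 21% | 2.89, 1.70, 25% |
| 2 | 1.96, 1.40, 16% | 2.29, 1.51, 20% |

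**Step 3: the same with 0.25 as a literal intra-cluster correlation.** √12.75 = 3.57 and √17.15 = 4.14, with type I error of 58% and 64%.

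**Step 4: a weak-clustering check.** At an intra-cluster correlation of 0.01 the design effects are 1.47 and 1.65, and the type I error is 11% and 13%.

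**The case against.** The strongest reply is that the correlation sentence is conditional. It says what is done where a child has repeated measures; it does not say that this is the whole correlation structure. The sampling and sizing text shows that the authors had facility clustering in view, and a model with children nested in facilities would satisfy both sections. Random-effect levels and variance estimators are usual content for an analysis plan, and this is a condensed article. This stands to the following extent: a reader might infer that facility clustering will be ignored, and the document does not say so. What remains is that the article is not silent on correlation. It names one level, and that level is not the one used for the sample size.

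A second reply concerns size. A reader who takes 0.25 at its label would infer intervals about four times too narrow. That reading does not reproduce the stated facility numbers, and a comparison with pure Poisson variance ignores what a child-level model already absorbs. Both points stand, which is why the lower range leads here. Adjustment for transmission intensity and other covariates could reduce the residual facility variation further, by an amount that the document does not allow one to estimate.

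A third reply is that not every listed analysis is affected alike. The historical series are monthly counts aggregated by facility, so the child is not the unit there and stable facility differences can cancel. In the per-protocol and dose analyses, exposure varies within a facility. This stands: the figures above apply to the child-level, intention-to-treat comparison of areas.

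**Conclusion.** The point holds for child-level comparisons of intervention and control areas, and it is conditional: if they are run as the Data analysis section is written, their standard errors are too small. The best-supported size is a factor of about 1.4 to 1.9 in Cameroon and 1.5 to 2.1 in Côte d'Ivoire, with type I error of roughly 16% to 36%. This rests on 0.25 being a coefficient of variation, on the under-5 rates over 18 months, on 20% loss, and on an assumed range for variation between children. The factors of 3.6 and 4.1 apply only if 0.25 is an intra-cluster correlation as labelled. Some inflation remains even with weak clustering, so the need for the change does not turn on how 0.25 is read. The document does not support the claim that the final intervals will be wrong, because an analysis plan that is not shown may add the facility level.

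**What to change.** Amend the Data analysis section so that every child-level comparison of intervention and control areas accounts for clustering by EPI facility. Either a facility random effect with child nested within it, or GEE or robust variance clustered on facility, would do. Name in advance a recognised small-sample correction, because there are only 9 and 5 control facilities. Several corrections are acceptable; the one chosen should also suit the analysis that combines the two countries. Apply the same rule at the interim analysis. In the Sample size section, state whether 0.25 is an intra-cluster correlation or a coefficient of variation.

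The report should add that, with one intervention and one control district per country, these intervals do not cover variation between districts. A facility term cannot supply that.

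The cost is a change of wording and one more level in the model. No data collection changes. The intervals become wider, and the analysis then matches the basis on which the study was sized.
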